#### Concealment mechanism {16b}

Patients, physicians, nurses, and the research coordinator will be kept strictly blinded as to individual group allocation and treatment. The intervention, active or placebo, will be provided to the clinicians responsible for administration in concealed containers. The clinical trial Pharmacy Research Technician will be responsible for the coding and labeling of all containers and instructions for administering the intervention will be identical for both control and amiodarone groups.

#### Implementation {16c}

The research coordinator will enroll recruited patients in the trial. The clinical trial Pharmacy Research Technician will assign enrolled individuals to an intervention using a secure web-based randomization system in accordance to the allocation sequence provided by the Methods Centre of The Ottawa Hospital Research Institute. Only the Pharmacy Research Technician at the Ottawa Hospital will see the randomization table and treatment assignments.

### Assignment of interventions: blinding

#### Who will be blinded {17a}

All members of the surgical care team including both in the operating room and on the surgery unit will be blinded to the intervention. The Pharmacy Research Technician preparing the medication will not be blinded to ensure appropriate allocation.

#### Procedure for unblinding if needed {17b}

If unblinding is required, physicians may login to the trial website to reveal the allocated treatment arm of the patient. The website will be available 24/7 for clinicians. It will also be accessible to the investigators to track if and when unblinding of participants occurs.

### Data collection and management

#### Plans for assessment and collection of outcomes {18a}

All data will be collected by trained research assistants. Data will be entered by the research assistants on password-protected files stored on the institutional network from the following: the electronic and paper case report forms developed and maintained specifically for this study; data from the Thoracics Morbidity & Mortality database (a clinical database from prospectively populated by the thoracic surgical team that is used to record complications of patients undergoing thoracic surgery at our institution) [3]; and The Ottawa Hospital Electronic Medical Records which will provide duplicate measurements to enhance data quality. Patient randomization and allocation data will be entered by the Research Pharmacy Technician.

#### .Plans to promote participant retention and complete follow-up {18b}

No additional strategies will take place to improve retention and completion by participants in this trial, in keeping with the pragmatic design of this study.

#### Data management {19}

Study data will be kept in password-protected files and stored on the institutional network with access restricted to the research team. A different user (i.e., one who has not performed the original data entry) will randomly select 20% of the collected CRF forms to review and verify for accuracy. Data will be coded by the research team for analysis. A Data Management Plan (DMP) developed in collaboration with the Methods Centre of the Ottawa Hospital Research Institute provides further details regarding data management procedures.

An independent Data Safety and Monitoring Board (DSMB) consisting of one pharmacist and three clinician scientists will perform data safety monitoring. The DSMB will be responsible for assuring that study participants in PREP-AF are not exposed to unnecessary or unreasonable risks and that the study is being conducted according to the highest scientific and ethical standards. Conduct of the DSMB is outlined in the PREP-AF DSMB Terms of Reference.

#### Confidentiality {27}

Patient’s personal health information will be kept confidential, unless release is required by law or permission is given by the patient. The consent form makes note that representatives of the local Research Ethics Board (REB) and/or Health Canada may review original medical records. A master list of the patient identifiers will be stored in a separate password protected, encrypted file on a secure institutional network at the Ottawa Hospital with restricted access to those involved as per the study protocol. All other electronic records will contain de-identified and coded data which will be password protected and encrypted.

#### Plans for collection, laboratory evaluation, and storage of biological specimens for genetic or molecular analysis in this trial/future use {33}

Not applicable to the nature of this study.

### Statistical methods

#### Statistical methods for primary and secondary outcomes {20a}

The primary end point of this study is feasibility so no in-depth statistical analysis is planned. However, for the anticipated full-scale trial to follow, we plan to conduct analysis using an intention-to-treat, considering all patients as randomized regardless of whether they received the randomized treatment. Patients will be administered the intervention while admitted to hospital following major thoracic surgery so we anticipate very few patients to crossover or be lost to follow-up. To reduce the risk of missing data, we will capture data from patient’s health records, surveys, and manual chart review. Any departures from the protocol will be documented in the participant file, reviewed, and compared quantitatively. Reasons for missing data will be recorded, and if missing data is >5%, multiple imputation methods will be used to address missing data in the analysis.

The statistical analysis will be performed using statistical software program R version 3.5.3. Continuous data that are normally distributed will be analyzed with an unpaired Student’s t-test. Non-continuous data will be analyzed with a chi-squared or Fisher’s exact test as appropriate. Level of significance will be determined by *p* < 0.05.

We plan to use this as a vanguard study. If a full-scale trial is completed, we plan to incorporate the results of this study into the data collection of a full-scale trial.

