## Introduction

### Background and rationale {6a}

Postoperative atrial fibrillation (POAF) is the most commonly sustained arrhythmia after thoracic non-cardiac surgery [1, 2]. We found it occurred in 17% of patients after lobectomy, 23% after pneumonectomy, and 12% after esophagectomy, making it the most common postoperative adverse event after thoracic surgery at our institution [3]. It is associated with increased postoperative morbidity, length of stay, ICU admission, and mortality [1, 2]. For example, POAF is associated with increased mortality risk after esophagectomy (from 4.8 to 8.1%, *p* = 0.04) [4]. Recently, the results of two large multicenter randomized controlled trials (RCTs) (POISE-1: metoprolol vs. placebo and POISE-2: aspirin vs. placebo) were analyzed with regard to the impact of POAF. Among 18,117 patients (mean age 69 years, 57.4% male), 404 had POAF (2.2%). The stroke incidence 1 year after surgery was 5.58 vs. 1.54 per 100 patient-years in patients with and without POAF. Patients with POAF also had an increased risk of death (incidence 31.37 vs. 9.34; aHR 2.51, 95% CI 2.01–3.14; *P* < 0.001) and MI (incidence 26.20 vs. 8.23; aHR 5.10, 95% CI 3.91–6.64; *P* < 0.001) [5]. Given the frequent incidence after thoracic surgery and marked impact of POAF, prophylaxis to prevent POAF is of interest.

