## Methods: participants, interventions, and outcomes

### Study setting {9}

This study will be conducted with the Division of Thoracic Surgery at The Ottawa Hospital, an academic teaching center in Ottawa, Ontario, Canada. At our center, approximately 200 patients undergo major thoracic surgery annually. Of which, 52% undergo a lobectomy, 25% a sublobar resection, 5% a pneumonectomy, and 11% an esophagectomy.

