Secondary clinical outcomes will include the incidence and severity of POAF (defined as an irregularly irregular atrial rhythm without clear P waves, recorded on a standard 12-lead electrocardiogram (ECG) that occurred in the immediate 30-day postoperative period [3]), and classified in severity by the Ottawa Thoracic Morbidity and Mortality (TM&M) system [3]; hospital length of stay; and incidence of other postoperative complications using the taxonomy of the TM&M definitions [3].

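### Length of stay has a named test only if it is normally distributed, and that comparison leaves out procedure type and the beta-blocker stratum

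*Protocol article*

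**What the plan says.** The protocol article, section {20a}, opens with a limit on its own ambition: "The primary end point of this study is feasibility so no in-depth statistical analysis is planned". It then names tests all the same. For continuous variables: "Continuous data that are normally distributed will be analyzed with an unpaired" Student's t-test. For the rest: "Non-continuous data will be analyzed with a chi-squared or Fisher’s exact test as appropriate". A threshold follows: "Level of significance will be determined by" p < 0.05. The same section plans to carry the results into a full-scale trial as a vanguard study.

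Section {12} lists the secondary clinical outcomes: incidence and severity of postoperative atrial fibrillation (POAF), then "hospital length of stay; and incidence of other postoperative complications using the taxonomy of the TM&M definitions". Only length of stay is continuous.

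On procedure, {20b} plans a subgroup analysis by procedure type. On design, {16a} stratifies randomization by beta-blocker use and by nothing else. Neither factor is mentioned in the treatment comparison. Section {14} aims for 80 randomized patients, and {8} allocates them 1:1.

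**The concern.** The two test rules do not cover all data. Continuous data that are not normal fall between them, and the one continuous clinical outcome is the variable most likely to land there. The analyst would then have to pick a method once the distribution is known, or use the t-test against the condition set for it.

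The named comparison is also unadjusted. Randomized patients range from lobectomy to esophagectomy, and stay plausibly differs between these operations. Procedure is known before randomization and must be recorded for eligibility; beta-blocker status must be recorded for stratification. Leaving both out gives away precision at no saving in data collection.

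At stake is a prespecified and reasonably precise length-of-stay estimate from a small trial whose data are meant to be reused. The primary feasibility criteria do not depend on it.

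**Working it through.** There is no figure to reproduce. Section {14} reports no sample size calculation, and the article gives no mean, spread or effect for length of stay.

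**1. Case mix.** Section {9} gives "52% undergo a lobectomy, 25% a sublobar resection, 5% a pneumonectomy, and 11% an esophagectomy". Sublobar resection is not randomized, so the eligible total is 52 + 5 + 11 = 68. For 80 patients, if risk score and consent do not vary by procedure:
- lobectomy 80 × 52/68 ≈ 61
- pneumonectomy 80 × 5/68 ≈ 6
- esophagectomy 80 × 11/68 ≈ 13

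**2. Chance imbalance.** Let X be the number of the 13 esophagectomies in one arm of 40, hypergeometric (80, 13, 40), ignoring blocks. A split of 9:4 or worse has probability 2·P(X ≥ 9) ≈ 22%. A split of 10:3 or worse has 2·P(X ≥ 10) ≈ 7%.

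**3. What procedure can remove.** Assume a log-scale SD σ within procedure and esophagectomy stays twice as long as the others. The between-procedure variance is p(1 − p)(ln 2)², with p = 13/80 = 0.1625: 0.1625 × 0.8375 × 0.480 ≈ 0.065.
- σ = 0.4: 0.065/(0.160 + 0.065) ≈ 29% of the total variance
- σ = 0.6: 0.065/(0.360 + 0.065) ≈ 15%

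**4. Simulation at this trial's size.** 40 per arm, log-normal stay rounded to days, 13 esophagectomies, 3000 runs per setting, two-sided 0.05. Assumed: median 5 days for lung resection, esophagectomy stay 1.5, 2 or 2.5 times longer, and a 25% shorter stay on treatment. Power in % for ratios 1.5 / 2 / 2.5:

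| log-SD | t-test | Mann-Whitney | log model with procedure |
|---|---|---|---|
| 0.4 | 79 / 65 / 52 | 82 / 74 / 68 | 86 / 88 / 87 |
| 0.6 | 45 / 40 / 35 | 50 / 46 / 45 | 52 / 56 / 54 |
| 0.8 | 27 / 24 / 23 | 34 / 31 / 30 | 36 / 36 / 36 |

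The gain of the adjusted log model over the t-test runs from about 7 points (79 to 86) to 35 points (52 to 87). With no effect, the t-test rejected in 3.6% to 5.3% of runs. Shapiro-Wilk rejected normality in at least one arm in 99% or more of runs in every setting.

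**5. Adding the beta-blocker stratum.** A separate run at 40 per arm, same effect, compared four methods at log-SD 0.4 and 0.6:
- t-test 66% and 40%
- Mann-Whitney 73% and 47%
- van Elteren by procedure and beta-blocker stratum 84% and 49%
- procedure-adjusted log model 86% and 54%

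Gains over the t-test are 84 − 66 = 18 and 49 − 40 = 9 points for van Elteren, and 86 − 66 = 20 and 54 − 40 = 14 for the log model. Null rejection was 4% to 6% for all four. At log-SD 0.6, van Elteren beats the unstratified rank test by only 2 points. A repeat with medians of 5, 7 and 10 days for lobectomy, pneumonectomy and esophagectomy moved no figure by more than 3 points.

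**The case against.** The strongest reply is that a journal article condenses a fuller protocol. The fallback for a skewed secondary outcome, the covariates and the handling of deaths are normal content of an analysis plan, and one may exist. The trial is a feasibility study that disclaims in-depth analysis, and the t-test sentence is not false: it limits itself to normal data. Much of this stands. A missing fallback alone would be detail left to another document. What remains is that the article does fix a set of tests and a significance level, and that set, as worded, misses its only continuous clinical outcome and leaves the comparison unadjusted.

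It can also be said that stratifying by procedure and beta-blocker use makes sparse cells, with about 6 pneumonectomies split over two strata, and that a cell with only one arm contributes nothing. That is true, but the gain survives in the simulation in step 5. The further point that vanguard pooling carries data forward, and that the full trial can specify its own test, also stands and lowers the severity.

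Three stronger readings are tempting and are not supported:
- A reader might infer that length of stay has no usable analysis. The t-test held its error rate under the assumed skewness, so it would be inefficient and outside its stated condition, but not invalid.
- A reader might infer that procedure is ignored. Section {20b} contradicts that; procedure is used, but only as a subgroup factor.
- A reader might infer from {6a} that in-hospital deaths would shorten stays enough to distort the result. The text says "POAF is associated with increased mortality risk after esophagectomy", from 4.8 to 8.1%. That contrasts patients by POAF status and is not stated to be in-hospital. Even taken at face value, 13 × 0.048 to 13 × 0.081 is about 0.6 to 1.1 deaths among the expected esophagectomies. The valid remainder is that no rule says how a death before discharge counts.

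**Conclusion.** The point holds as a badly fixed sentence with a modest consequence. As written, {20a} would probably leave the length-of-stay method to be chosen after the data are seen, and its named comparison uses neither procedure nor the randomization stratum. The cost is precision and prespecification, not validity.

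The size is about 9 to 20 power points over the t-test in the two settings that included both stratification factors, and 7 to 35 points for procedure adjustment across the wider grid. These figures rest on assumed log-normal stays, an assumed ratio between procedures and an assumed 25% effect. That stay is skewed and depends on procedure is plausible, but the article gives no data on either. If procedure had little influence on stay, most of the gain from adjustment would disappear and the prespecification gap would remain. Severity is low: this is a secondary outcome, and no feasibility criterion turns on it.

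**What to change.** In {20a}, name one analysis of length of stay that applies whatever its distribution and accounts for planned procedure and beta-blocker stratum. Two options serve:

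- **A linear model on log stay** with treatment, planned procedure and beta-blocker stratum, reported as a ratio of geometric means with 95% CI. This gives estimate and interval directly and copes better with small procedure groups.
- **A van Elteren test** stratified by the same two factors. It allows deaths to be ranked worst, but an ordinary Hodges-Lehmann difference does not match the stratified test and needs a numeric stay for each death, so the accompanying estimate must be defined with care.

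In this feasibility trial, report mainly the estimate and its interval. Add a sentence on how a death before discharge is counted, and give the number of such deaths by arm. Use planned rather than performed procedure, since it is fixed before randomization. The t-test sentence can stay for other variables.

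The cost is two or three sentences and no new data. The downside is small: the effect is expressed as a ratio or a median shift, not as a mean difference in days.

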### Assignment of interventions: allocation

#### Sequence generation {16a}

After written informed consent is obtained, high-risk patients will be randomly assigned to either the intervention or control group by the clinical trial Pharmacy Research Technician using a secure web-based randomization system at the Methods Centre of The Ottawa Hospital Research Institute. Randomization will be stratified according to pre-randomization beta-blocker use. Allocation bias will be prevented by using a randomization table with variable blocks of 4 and 6.

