#### Methods for additional analyses (e.g., subgroup analyses) {20b}

Additional subgroup analysis by procedure type will be conducted.

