#### Methods in analysis to handle protocol non-adherence and any statistical methods to handle missing data {20c}

The primary end point of this study is feasibility so no formal statistical analysis is planned. However, for the anticipated full-scale trial to follow, we plan to conduct analysis using an intention-to-treat, considering all patients as randomized regardless of whether they received the randomized treatment. Patients will be administered the intervention while admitted to hospital following major thoracic surgery so we anticipate very few patients to crossover or be lost to follow-up. To reduce the risk of missing data, we will capture data from patient health records, surveys, and manual chart review. Any departures from the protocol will be documented in the participant file and reviewed quantitatively to compare reasons. Reasons for missing data will be recorded, and multiple imputation methods will be used to address missing data in the analysis.

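### The plan disclaims formal analysis yet names unstratified tests at p < 0.05 without saying which trial they serve, and gives no safeguard for reusing the vanguard data in the full trial

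*Protocol article*

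**What the plan says.** All references are to the protocol article.

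- **Disclaimers.** Statistical methods {20a} opens by saying that no in-depth analysis is planned because the end point is feasibility. Section {20c} is firmer: "The primary end point of this study is feasibility so no formal statistical analysis is planned".
- **Named tests.** After a passage on how the anticipated full-scale trial would be analysed, {20a} continues in a new paragraph: "Continuous data that are normally distributed will be analyzed with an unpaired Student’s t-test". For other data, "Non-continuous data will be analyzed with a chi-squared or Fisher" tests are named. The threshold follows: "Level of significance will be determined by *p* < 0.05". No sentence says which trial these tests serve.
- **Subgroups.** Section {20b}: "Additional subgroup analysis by procedure type will be conducted".
- **Reuse.** Section {20a} ends by calling the study a vanguard. If a full-scale trial is completed, "we plan to incorporate the results of this study into the data collection of a full-scale trial". Nothing is said about alpha, or about who may see by-arm results in the meantime.
- **Strata.** Sequence generation {16a}: "Randomization will be stratified according to pre-randomization beta-blocker use". Trial design {8} gives the reason: beta-blockers are held to protect against POAF. None of the named tests uses the strata.
- **Context.** Outcomes {12} makes feasibility primary, with several numeric thresholds, and POAF secondary. Interim analyses {21b} ties the DSMB's recommendations to safety data. Section {11b} has the allocation revealed for each randomised patient who develops POAF.

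**The concern.** Read literally, the sections conflict: no formal analysis, but significance tests at a fixed level. An analyst could follow either.

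The conflict matters more because the same patients may be counted again. If POAF is compared by arm at p < 0.05, published, and the 80 patients then enter the full trial, the first comparison can act as an interim efficacy look for which no alpha has been set aside. If the by-arm result also influenced the decision to go on, the pooled estimate would be biased. In the other direction, a non-significant result from very few events could discourage a worthwhile trial.

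The strata are a separate and smaller matter. Randomising within beta-blocker strata and then analysing without them gives up part of what the stratification bought.

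**Working it through.** **Inputs from the protocol article.** 80 to be randomised (Sample size {14}), 1:1, so 40 per arm. POAF in the high-risk group 12.3%, and a risk ratio of 0.22 giving 2.7% and an NNT of 10.4 (Prediction of POAF). Threshold p < 0.05 ({20a}); sidedness is not stated, and two-sided is assumed.

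**The plan's own figures.** 0.123 × 0.22 = 0.0271, or 2.7%. NNT = 1/(0.123 − 0.027) = 10.4. Both reproduce. The article gives no power or sample size calculation to check.

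**1. What a test on 80 patients could show.**
- Expected events: 40 × 0.123 = 4.9 and 40 × 0.027 = 1.1, about 6 in all.
- The nearest whole-number result, 5/40 against 1/40, gives a Fisher p of 0.20.
- Exact power (sum of binomial probabilities over all tables with p < 0.05) for 12.3% against 2.7%: Fisher 17.5%, uncorrected chi-squared 41%.
- If risk is only halved (12.3% against 6.15%): Fisher 7%, chi-squared 17%.
- For comparison, 80% power for 12.3% against 2.7% needs 117 per arm, or 138 with continuity correction.

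**2. Type I error if success could be declared at either look.** Let Z₁ be the statistic at 80 patients and Z₂ the one on the pooled N. Under the null they are bivariate normal with correlation √(80/N), and the overall error is 1 − P(|Z₁| < 1.96 and |Z₂| < 1.96). N is assumed, since no full-trial size is given.

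| Assumed total N | Correlation | Overall two-sided error |
|---|---|---|
| 160 | 0.707 | 8.3% |
| 234 | 0.585 | 8.8% |
| 400 | 0.447 | 9.2% |
| 800 | 0.316 | 9.5% |
| 1600 | 0.224 | 9.6% |

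This takes each look at its nominal 5%. Fisher's test at 40 per arm is conservative: at a common rate of 12.3% it rejects in 2.2% of trials. With Fisher at the first look, the overall error is at most 2.2 + 5 = 7.2%. For scale, an O'Brien-Fleming-type boundary would allow about 0.0008 at the first look when N = 234 and about 0.00001 when N = 400.

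**3. Type I error if only the pooled test is confirmatory.** If the vanguard result cannot support an efficacy claim and does not drive progression, there is one test at 0.05, and the error is 5%.

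**4. Cost of ignoring the strata.** For a share q on beta-blockers with POAF rates a (off) and b (on), let p = (1 − q)a + qb. The stratified-to-unstratified variance ratio is 1 − q(1 − q)(a − b)²/[p(1 − p)]. The article gives neither q nor a and b, so they are assumed.

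| q | a | b | p(1 − p) | q(1 − q)(a − b)² | Ratio |
|---|---|---|---|---|---|
| 0.30 | 0.15 | 0.06 | 0.1079 | 0.0017 | 0.984 |
| 0.30 | 0.18 | 0.04 | 0.1190 | 0.0041 | 0.965 |
| 0.40 | 0.20 | 0.04 | 0.1175 | 0.0061 | 0.948 |

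The loss is about 2 to 5% of variance. In simulations under the null at 150 per arm (beta-blocker use 30 to 50%, risk ratio 0.25 to 0.5), the unstratified chi-squared test rejected in 4.4 to 4.9% of trials, against 4.9 to 5.0% without a stratum effect. That is slightly conservative, not inflated.

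**5. Procedure subgroups.** Study setting {9} gives 52% lobectomy, 5% pneumonectomy and 11% esophagectomy. Scaled to 80 (52:5:11 of 68), that is about 61, 6 and 13 patients. These are all-patient proportions applied to a score-selected group, so they are a rough guide only.

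**The case against.** The strongest reply is that the article never says POAF will be tested by arm in these 80 patients. The test paragraph follows the turn to the full-scale trial, both {20a} and {20c} disclaim serious analysis, POAF is secondary, the DSMB acts on safety data, and pooling is conditional on a full trial being completed. How that trial would spend its alpha belongs in its own protocol. Low power is no defect in a feasibility study that claims none.

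Much of this stands. A reader might infer that the plan commits to an undeclared efficacy look that nearly doubles the type I error. The document does not support that: no passage allows efficacy to be declared at the vanguard stage or makes progression depend on by-arm POAF. A reader might also take the unstratified tests as a further source of false positives. They are not; they err slightly the other way.

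The ambiguity remains. The test paragraph is separate, sits in the section on this trial's own primary and secondary outcomes, and names a specific software version, so applying it to this trial is at least as natural a reading. On the other reading, the full trial's analysis is set down as unstratified tests, and the vanguard data still enter it without a safeguard. Nor does any passage say that progression rests on feasibility alone. Either way the text needs a clarifying sentence.

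One practical limit also stands. Since {11b} reveals allocation for each POAF case, withholding a by-arm table cannot fully mask the efficacy result from the study team.

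**Conclusion.** The point holds in limited form. The firm finding is a contradiction in the text: formal analysis is disclaimed, tests at p < 0.05 are named, and the trial they serve is not identified, in a study whose data may be reused without any stated protection.

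The type I error consequence is conditional. It is about 8 to 10% at nominal levels (two-sided tests, total N of 160 to 1600 assumed), and at most about 7% if the first look uses Fisher's test, but only if success could be declared at either look. Otherwise it is 5%. Power of about 18% is no fault of the design; it shows that a by-arm p-value for POAF would be uninformative here. Ignoring the strata costs a little precision, about 2 to 5% of variance under assumed prevalence and rates, and is a secondary point. The correction should be made because it is cheap now and cannot be made cleanly once by-arm results are out.

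**What to change.** Amend the wording of {20a}, {20b} and {20c}:

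1. Say which trial the named tests apply to. For this one, state that clinical outcomes are reported descriptively, as estimates with 95% confidence intervals and without between-arm efficacy tests at p < 0.05.
2. State that progression to the full trial rests only on the feasibility criteria in Outcomes {12}.
3. For the case that the data are pooled, choose one rule in advance. Either withhold by-arm efficacy summaries until the full trial reports, leaving by-arm safety data with the DSMB, or declare the look a formal interim analysis with an alpha-spending boundary. Acknowledge that the unblinding of POAF cases under {11b} limits how far withholding can mask the result.
4. Wherever arms are compared, in this trial or the next, use an estimate stratified by beta-blocker use, such as a Mantel-Haenszel risk difference or ratio, with a 95% confidence interval.
5. Report procedure subgroups as counts.

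The cost is a few sentences. The feasibility paper loses its by-arm efficacy p-value and, if summaries are withheld, also the by-arm efficacy estimate.
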